#### Follow-up

Outcome measures will be collected by self-report, postal questionnaire before randomisation and at 3, 6, 9, 18 and 36 months (Figure 
1). Therefore, adherence to exercise will be measured twice throughout the early phase (0 to 6 months) and three times during the maintenance phase of the exercise interventions (9 to 36 months). Non-responders will be followed up using our standardised CTU follow-up procedures for trials. This comprises a questionnaire, a reminder postcard at two weeks and a further copy of the questionnaire at four weeks. For participants who do not respond to any of these reminders, we will aim to collect minimum outcome measure data via telephone (by research nurses who are blind to treatment allocation) and post at key outcome time-points (6 months, 18 months and 36 months) in order to try to capture primary outcome data and to minimise missing data. Quality assurance processes within the CTU will ensure training and auditing of the research nurses conducting minimum data telephone calls. In order to reduce participant burden the 3 and 9 month questionnaires will be slightly shorter than those at 6, 18 and 36 months and as direct measures of physical activity may themselves increase physical activity similar measures of physical activity will be used in each intervention group. Table 
2 includes a list of all measures and the time-points at which they will be collected.

**Table 2 T2:** Outcome measures

**Data collection**	**Measurement scale**	**Time points (months)**
*Participant characteristics*		
Age	Years	0,3,6,9,18,36
Gender	Female/Male	0,3,6,9,18,36
Weight	Stones and lbs or Kilograms	0,3,6,9,18,36
Height	Feet and inches or centimeters	0
Marital status	Married/separated/divorced/widowed/cohabiting/single	0
*Work factors*		
Current/most recent job title	Free Text	0,6,18,36
Currently in a paid Job	Yes/No	0,6,18,36
Working hours	Working full time (30 hours or more per week)/working part time (29 hours or less per week)/	6,18,36
Time off because of knee pain including time off to visit any health care professional	Yes/No (during last 6 months)	6,18,36
How many days weeks, weeks or months were you absent from work due to knee problem	Number of days/weeks/months (during last 6 months)	6,18,36
*Knee Problem*		
Knee with most discomfort	Tick boxes for left or right	0,3,6,9,18,36
Duration of knee problem	In the last 12 months/More than 1 year but less than 5 years ago/More than 5 years but less than 10 years ago/I have had this knee problem for more than 10 years	0
Global assessment of change in knee problem	Completely recovered/much better/better/no change/worse/much worse (since first seen by the physiotherapist)	3,6,9,18,36
Knee pain^α^	0–20	0,3,6,9,18,36
Stiffness^α^	0-8	
Function^α^	0 - 68	
	(WOMAC [48])	
Illness perceptions^α^		0,3,6,
- Consequences	0-10	
- Timeline	0-10	
- Personal control	0-10	
- Treatment control	0-10	
- Identity	0-10	
- Concern	0-10	
- Understanding	0-10	
- Emotional response	0-10	
	(IPQ-brief modified for knee pain [54])	
*Physical Activity & Exercise*		
Experience of exercise	Personal experiences of exercise	0
Use of local facilities^α^	Use of local facilities for physical activity in the last 7 days	0,3,6,9,18,36
Self-efficacy for exercise^α^	0-10 (SSE scale [55])	0,3,6
Outcome expectations for exercise^α^	1-5 (OEE-2 [56])	0,3,6
Physical activity^α^	0-400+ (PASE [51])	0,3,6,9,18,36
Exercise adherence and treatment credibility	Confidence in and adherence to treatment plan	3,6,9,18,36
Accelerometry^α^	Average counts per minute	For a sub-sample of participants 0,3,6,9,18,36
	Meeting physical activity guidelines [60]	
*General health and well being*		
Depression^α^	0-24 (PHQ8 [58])	0,3,6,18,36
Anxiety^α^	0-21 (GAD7 [57])	0,3,6,18,36
Quality of life^α^	-0.59-1 (EQ-5D-3 L [59])	0,3,6,9,18,36
Body manikin (pain)	Body area shaded to represent pain last a day or longer in the last 4 weeks	0
Co-morbidity	Tick boxes for key co-morbidities	0
*Managing your knee problem*		
Current medication for knee problem	Prescribed and over the counter medications (with dosage and length of supply)	0,3
Prescribed medication for knee problem	Prescribed medications in the last 6 months/12 months/18 months (with dosage and length of supply)	6,18,36
Cost of over the counter treatments/appliances	e.g. painkillers, anti-inflammatory drugs, TENS machine, hot and cold packs, knee supports (£ in the last 6 months/12 months/18 months)	6,18,36
Costs for use of local facilities/opportunities involving physical activity	(£ in the last 6 months/12 months/18 months)	6,18,36
Healthcare Utilisation	Contact with NHS and private healthcare professionals, number of visits/inpatient stays, types of investigations/treatments in the last 6 months/12 months/18 months	6,18,36

Key: EQ-5D-3 L = Quality of Life; GAD 7 = Generalized Anxiety Disorder 7; IPQ – Brief = The Brief Illness Perception Questionnaire; OEE-2 = Outcome Expectations for Exercise Scale - 2; PASE = Physical Activity Scale for the Elderly; PHQ8 = Patient Health Questionnaire 8; SEE = Self-Efficacy for Exercise Scale; WOMAC = Western Ontario and McMaster Universities Arthritis Index. α = Measure used as an outcome to test for clinical effectiveness (along with Body mass index (BMI) and the OMERACT-OARSI responder criteria
[16,17], which are not indicated on this table as derived by combining individual measures of height and weight for BMI and WOMAC pain and function with global assessment of change for the OMERACT-OARSI responder criteria).

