#### Costs

Information on resource use and time off work will be collected from patient-completed questionnaires at 6 months, 18 months and 36 months. Health sector costs include primary and secondary care contacts, investigations, pain medications and contacts with other health care professionals. The cost of the interventions will also be determined taking into account any additional resource use required to deliver those interventions such as additional physiotherapy visits and telephone contacts and any additional equipment (e.g. pedometers) supplied to patients. The cost of the advice and information booklet will not be included as this will be given to all trial participants and will therefore be cancelled out in the cost analysis. Questions on patients’ personal expenditure will concentrate on private health care use and over-the-counter treatments. Due to the lack of nationally representative unit cost estimates for private health care, this care will be costed as the NHS equivalent in the base-case. Patient reported costs for over-the-counter treatments will be used.

Resource use will be multiplied by unit costs obtained from standard sources and health care providers including the British National Formulary (BNF), Unit Costs of Health and Social Care and NHS Reference costs
[74-76]. Productivity costs will be calculated using data collected on employment status at every time point and days off work due to knee pain. For those in paid employment, information on occupation, further details of typical work activities and the nature of their employment (full time or part time) will be requested. The average wage for each respondent will be identified using UK Standard Occupational Classification coding
[77] and annual earnings data for each job type
[78]. The analysis will use the human capital approach, and the self-reported days of absence will be multiplied by the respondent-specific wage rate.

The data for costs are likely to have a skewed distribution therefore the plan is to explore the nature of the distribution of costs. If the data are not normally distributed, then a non-parametric comparison of means, using bootstrapping, will be undertaken
[79].

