#### Cost-effectiveness analysis

The primary economic analysis will be conducted at 18 months, with additional analysis at 36 months. An intention-to-treat analysis will be undertaken. Multiple imputation techniques will be used to deal with missing EQ-5D-3 L scores and resource use data, ensuring that all eligible trial participants are included in the base case economic evaluation. All estimates will be presented as means with 95% confidence intervals.

The base case cost analysis will adopt a NHS and personal social services (PSS) perspective. A broader costing perspective will be considered in a sensitivity analysis, taking into account NHS/PSS costs, patients’ personal expenditure and costs associated with work loss. All costs and outcomes beyond 12 months will be discounted at the standard UK rate of 3.5%.

The estimation of cost-effectiveness within this trial will focus on the principles of dominance and extended dominance. Dominance is a straightforward concept; if an intervention is less effective and more costly than at least one of its comparators, it is not included for further consideration with regard to the estimation of cost-effectiveness. Extended dominance is applied in incremental cost-effectiveness analysis when an intervention is less effective and more costly than a linear combination of two other strategies; the purpose is to remove from consideration those strategies whose costs and benefits are improved by a mixed strategy of two other alternatives. The practical application of cost-effectiveness analysis is to compare an intervention with the next most effective strategy, therefore strategies are ordered in term of QALYs from least to greatest. Failure to remove all dominated or extendedly dominated strategies may lead to comparisons that are not with the next best alternative but with irrelevant alternatives.

The robustness of the results will be explored using sensitivity analysis. Deterministic sensitivity analysis will explore uncertainties in the methods employed to analyse the data, for example a complete case analysis as an alternative to using an imputed data set, any assumptions made in the analysis and the generalisability of the results to other settings.

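### Work absence is asked about for only 12 of the first 18 months and 18 of all 36 months, so the broader-perspective cost analysis adds part-period productivity costs to full-period healthcare costs

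*Protocol article*

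**What the plan says.** All of this is in the protocol article.

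- **Absence items (Follow-up, Table 2, work factors).** Two rows are collected at 6, 18 and 36 months. One asks whether any time was taken off: "Yes/No (during last 6 months". The other asks how much: "Number of days/weeks/months (during last 6 months". Both have a single fixed look-back.
- **Other resource items (same table).** Prescribed medication, over-the-counter costs, facility costs and healthcare use are collected at the same three points, with the look-back "in the last 6 months/12 months/18 months". For healthcare use the row reads "number of visits/inpatient stays, types of investigations/treatments in the last 6 months/12 months/18 months".
- **Source of the data (Costs).** "Information on resource use and time off work will be collected from patient-completed questionnaires at 6 months, 18 months and 36 months".
- **Costing rule (Costs).** "the self-reported days of absence will be multiplied by the respondent-specific wage rate".
- **Horizons (Cost-effectiveness analysis).** "The primary economic analysis will be conducted at 18 months, with additional analysis at 36 months". The base case takes the NHS and personal social services perspective. Work loss enters only in a sensitivity analysis with a broader perspective, where it is combined with those costs and patients' own spending.

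**The concern.** The intervals between the three economic questionnaires are 6, 12 and 18 months. Four resource rows have look-backs of exactly those lengths, so together they cover the follow-up without a gap. The two absence rows do not, although they are collected on the same occasions. Because the table varies the window elsewhere, the fixed 6 months is hard to read as shorthand for the time since the last economic questionnaire. Table 2 has no absence item at 3 or 9 months that could fill the gap.

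The costing rule then takes the reported days as they stand. Applied as written, a month that nobody was asked about adds nothing to the productivity cost. The broader perspective would add healthcare and personal costs for the full 18 or 36 months to productivity costs for only part of that time. A reader comparing the components, or the totals between arms, would not be comparing like with like.

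**Working it through.** The article gives no figure for recall coverage, so there is none to reproduce. The check is a count of months.

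**Inputs.** Questionnaires at t = 6, 18 and 36 months (Costs; Table 2). Absence look-back 6, 6 and 6 months; look-back for the other resource rows 6, 12 and 18 months (Table 2). Horizons 18 and 36 months (Cost-effectiveness analysis).

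**Coverage.** Each questionnaire observes the months from t minus look-back to t.

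| Questionnaire | Absence items | Other resource items |
|---|---|---|
| 6 months | 0-6 | 0-6 |
| 18 months | 12-18 | 6-18 |
| 36 months | 30-36 | 18-36 |

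- To 18 months: absence is observed for 6 + 6 = 12 months. Months 6-12 are missing: 6/18 = 33%.
- To 36 months: absence is observed for 6 + 6 + 6 = 18 months. Months 6-12 and 18-30 are missing: (6 + 12)/36 = 50%.
- Other resource items: 18 of 18 and 36 of 36 months, no gap.

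**Effect on the cost.** Let r be the mean monthly absence in the unasked months divided by that in the asked months. The documents do not give r. Before discounting, the share of true absence that is captured is 12/(12 + 6r) at 18 months and 18/(18 + 18r) = 1/(1 + r) at 36 months.

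| Assumed r | Captured by 18 months | Captured by 36 months |
|---|---|---|
| 0.5 | 12/15 = 80% | 1/1.5 = 67% |
| 1 (even accrual) | 12/18 = 67% | 1/2 = 50% |
| 2 | 12/24 = 50% | 1/3 = 33% |

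If absence accrues evenly within every arm, each arm's cost is scaled by the same factor, and so is any difference between arms.

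**Direction between arms.** The error in a between-group difference is whatever difference in absence arises in months 6-12 and 18-30. The documents contain nothing from which to estimate it.

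**The case against.** **Reach.** Work loss is outside the base case. The base-case cost-utility result and all clinical outcomes are untouched. This stands, and it limits the importance of the point.

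**Costing the gaps as zero is an inference.** The Costs section is silent on the unasked months, and an article may leave scaling to a health economics plan that is not shown. The Cost-effectiveness analysis section also plans multiple imputation for missing resource-use data. This stands in part. Such a plan could settle the costing, but it could not recover answers to a question never put. The imputation described does not clearly extend to periods about which no participant was asked. The recall windows are fixed in Table 2, not left out.

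**A short recall may be deliberate.** Days absent over 18 months are harder to remember than over 6. That is a fair reason for a short window, but the unasked months then need a stated method.

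**Bias against the new arms.** A reader might infer that the gaps penalise the two new interventions, because extra appointments fall in the observed early months and later avoided absence is missed. The documents do not support this:

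- Time off for healthcare visits is mentioned in the yes/no row. The costed row asks about absence due to the knee problem.
- Individually Tailored Exercise ends by 12 weeks (Table 1), so only Targeted Exercise Adherence is delivered across the whole of months 0-6.
- The Background reports that the benefits of exercise declined over time in earlier work. With no later difference between arms, the incremental productivity cost is unchanged. With more later absence in a new arm, the error favours that arm.

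**Employment status.** A reader might also see an error in "Productivity costs will be calculated using data collected on employment status at every time point", since Table 2 has paid-job status at 0, 6, 18 and 36 months but not at 3 or 9. The phrase reads naturally as the economic questionnaires, all of which include it. This is clerical and does not affect the costing.

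**Conclusion.** The point holds within a limited scope. Two rows of Table 2 have a look-back that does not match the interval since the previous economic questionnaire, while four comparable rows do match. Absence goes unmeasured for 33% of the 18-month horizon and 50% of the 36-month horizon. Those fractions rest only on Table 2 as printed.

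The size of the undercount needs two further conditions: that the costing rule is applied without scaling, and that absence accrues evenly. Productivity costs, and any between-group difference in them, are then about two-thirds of the true value at 18 months and one-half at 36 months. If absence is not even, the captured share moves as the table of r shows. No direction of bias between arms can be claimed. The consequence is confined to the broader-perspective sensitivity analysis. It is worth correcting because the stated rule gives a total on mixed time bases and the remedy is cheap.

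**What to change.** - **Questionnaires not yet in use.** Ask both absence items about the last 12 months in the 18-month questionnaire and the last 18 months in the 36-month questionnaire, as for the other resource items. The cost is a wording change on two forms. The downside is a longer recall period, already accepted for healthcare use.
- **Questionnaires already in use.** Keep the 6-month window, because a change part-way would mix recall periods between participants. State in the economic analysis that absence in months 6-12 and 18-30 will be estimated from the adjacent observed rates or imputed, not costed as zero. Report the part-period total alongside so that the effect of the assumption is visible. The cost is a short addition to the analysis text and one extra result. The downside is that the estimate depends on an assumption the data cannot test.
- **Clerical.** Name the months at which employment status is collected (0, 6, 18 and 36) in the Costs section.

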#### Adverse events

The occurrence of adverse events from all interventions will be monitored and assessed using case report forms, contact with the trial co-ordinator, physiotherapist report, and follow-up questionnaires. A common adverse event from unaccustomed exercise and physical activity is temporary, mild muscle soreness. Physiotherapists delivering the interventions will advise participants about how to manage such symptoms.

Each physiotherapy site will report any serious adverse event (SAE) experienced by a trial participant immediately to the trial Chief Investigator that may possibly be related to either the interventions or the trial procedures. The Chief Investigator will assess whether the event was related to or resulted from any of the BEEP trial interventions or procedures, according to the process laid out in the BEEP trial Standard Operating Procedure for SAEs. Any SAE considered to be related to the trial procedures or interventions will be reported to the main Research Ethics Committee by the Chief Investigator within 15 days of her becoming aware of the event. In addition, all such events will be reported to the trial sponsor, Trial Steering Committee and Data Monitoring Committee.

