### Intervention 1: usual physiotherapy care

Usual physiotherapy care consisting of advice and exercise is the most appropriate control group for the BEEP trial given that randomised trials
[15] and systematic reviews
[6] consistently show that interventions that include exercise are superior to those which do not. We are not using an attention control group as this trial is designed explicitly as a pragmatic trial, building on evidence about the effectiveness of exercise interventions. Clinical practice guidelines
[2] recommend that all patients with OA are advised to exercise and in UK clinical practice, patients are seen in relatively few treatment sessions, and provided with brief relatively standardised exercise programmes that do not take into account differences between individual patients. Our ABC knee study described usual UK physiotherapy practice and formed the basis for the BEEP trial protocol for usual care
[14].

The BEEP trial protocol for usual physiotherapy care will consist of advice and lower limb exercise previously tested and shown to be more effective in the short-term than advice alone
[15]. Exercises will be selected from an agreed template of commonly prescribed exercises (printed from the commonly used PhysioTools computer software), including specific lower limb muscle strengthening (non-weight-bearing and weight-bearing) and range of movement or stretching exercises. Patients will receive up to 4 one-to-one treatment sessions with a physiotherapist over a period of 12 weeks, during which advice to continue to exercise will be provided but individualisation, progression and supervision of the exercise programme will be minimal, as in usual care. Other interventions used frequently by physiotherapists such as manual therapy and electrotherapy will be permitted as per usual care and they will be recorded on case report forms but the emphasis of the intervention will be supporting the patient to self-care and to follow the advice and exercise programme at home. This usual care protocol matches usual UK practice in that it focuses on lower limb strengthening exercise, relies on self-report rather than the use of exercise diaries to monitor adherence and progress, is delivered over few treatment sessions and thus has limited opportunity for individualisation, supervision or exercise progression and does not offer refresher or booster sessions following the end of the episode of care
[14].

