[19], and focuses on individualised strengthening (non-weight-bearing and weight-bearing), stretching and balance exercise for lower limb rehabilitation and functional task training. The patient and physiotherapist will define lower limb functional and exercise goals and agree targets that are reviewed and progressed. Individualisation is based on the findings of the physiotherapy assessment of each individual, including biomechanical and physiological observations, pain responses to specific exercises and starting levels of strength, range of movement and balance. Exercises will be prescribed for each individual and participants will be given their own individual print-out of their specific exercise prescription (selected and printed from PhysioTools computer software) and these exercise prescriptions (and print-out instructions) will change over time as the exercise programme is progressed. Physiotherapists will encourage exercise behaviour change using self-monitoring through use of an exercise diary to record their adherence with their lower limb exercise prescription (see Additional file
3). In order to provide greater opportunity for individualisation, supervision and progression of exercise, patients will receive between 6 to 8 one-to-one treatment sessions with a physiotherapist. There will be no scheduled follow-ups (refresher or booster sessions) with the physiotherapist beyond 12 weeks.

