[45] and therefore we will include pedometers within the suite of options for physiotherapists to give participants who wish to target increases in walking activity.

The BEEP trial protocol for Targeted Exercise Adherence will begin with a focus on the lower limb (as in the Individually Tailored Exercise group) but transitions to focus increasingly on general physical activity adherence over time. In addition to prescribing an individualised, progressed and supervised lower limb exercise programme, physiotherapists will assess patients’ current general physical activity levels, their intentions to increase their physical activity levels, their attitudes to exercise for knee pain and general health and explore their individual barriers and potential facilitators to exercise. This group will receive 4 treatments up to week 12 and a further 4 to 6 contacts from week 12 through to 6 months (a total of 8 to 10 treatment contacts). In the first 4 treatments, the aim will be for participants to initiate and progress an exercise programme with supervision that will include lower limb and general exercise, and to identify (with the support of the physiotherapist) general physical activity opportunities within the local community that are suitable for, and interest, the individual. Pro-active follow-up from the physiotherapist will take place from week 12 through to 6 months, using choices of telephone and face-to-face contact, providing an additional 4 to 5 contacts with each participant. The aim is to enhance long-term exercise adherence, promote increased general physical activity and encourage participants to develop an exercise ‘habit’, shifting the focus away from lower limb exercise in the earlier treatment sessions and towards sustainable lifestyle changes in physical activity in later treatment sessions. The follow-up sessions will ascertain and promote exercise adherence, increases in physical activity levels, support patients to integrate exercises into their activities of daily living, allow repetition and amendment of the exercise programme based on individuals’ experiences or concerns and progression at a pace suitable for the individual. The adherence enhancing ‘toolkit’ contains different educational and behavioural tools for facilitating physical activity behaviour change, selected for use based on an individualised assessment of each patient. As our Cochrane review identified that no one model of behaviour change was superior for facilitating adherence to exercise for chronic musculoskeletal pain, different theoretical models have underpinned the development of the toolkit, including self-efficacy

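### Adverse-event capture may differ by arm, because two of four sources and the serious-event route depend on unequal physiotherapist contact, and the questionnaire source is not shown in Table 2

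*Protocol article*

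**What the plan says.** The Adverse events section names four sources: events "will be monitored and assessed using case report forms, contact with the trial co-ordinator, physiotherapist report, and follow-up questionnaires". The same section makes each physiotherapy site responsible for reporting serious events that may be related to the interventions or trial procedures to the Chief Investigator. It describes no other route for serious events. The Interventions and Other data sections describe the case report forms as physiotherapy forms.

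Planned physiotherapist contact differs by arm:

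- Usual care: "Patients will receive up to 4 one-to-one treatment sessions with a physiotherapist over a period of 12 weeks".
- ITE: "patients will receive between 6 to 8 one-to-one treatment sessions with a physiotherapist", and "There will be no scheduled follow-ups (refresher or booster sessions) with the physiotherapist beyond 12 weeks".
- TEA: "This group will receive 4 treatments up to week 12 and a further 4 to 6 contacts from week 12 through to 6 months". A later sentence in the same section repeats the point: "Pro-active follow-up from the physiotherapist will take place from week 12 through to 6 months".

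Table 1 agrees and shows no follow-up after 12 weeks for usual care or ITE.

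The Follow-up section sends postal questionnaires to all participants at 3, 6, 9, 18 and 36 months and states that Table 2 "includes a list of all measures and the time-points at which they will be collected". No row of Table 2 is an adverse-event item. The table key declares two omissions, BMI and the OMERACT-OARSI responder criteria, "which are not indicated on this table as derived by combining individual measures of height and weight for BMI" and, for the responder criteria, from WOMAC and global change. The Other data section lists further questionnaire variables, and adverse events are not among them. On analysis, the statistical section says only that information on adverse events will be reported.

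**The concern.** When events are recorded at treatment contacts, an arm with more contacts, or with contacts over a longer period, has more opportunities to record the same underlying events. Here the two experimental arms have more contacts than the control arm, and one of them is followed by a therapist for about twice as long. Each arm is also treated by different therapists who cannot be blinded.

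The usual protection is a source that asks every participant the same question on the same schedule. The follow-up questionnaires could do this, and the Adverse events section counts on them. Trial co-ordinator contact does not depend on treatment sessions, but it has no stated schedule. Table 2 does not show the questionnaire item, so a reader cannot tell what is asked or when.

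The Background cites concern among patients and physiotherapists about the safety of exercise as part of the trial's rationale, so published event counts by arm will be compared even if no test is done. With unequal capture, the more intensive programmes could look less safe than they are. Mild events in usual care, such as muscle soreness that leads to no healthcare visit, could be under-counted.

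**Working it through.** **Inputs** (Table 1 and the three Intervention sections)

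| Arm | Planned contacts | Treatment period |
|---|---|---|
| Usual care (UC) | up to 4 | up to 12 weeks |
| ITE | 6 to 8 | up to 12 weeks |
| TEA | 8 to 10 (4 by week 12, then 4 to 6) | up to 6 months |

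**Step 1. Contact ratios, with usual care at its maximum of 4**

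- TEA/UC: 8/4 = 2.0 to 10/4 = 2.5.
- ITE/UC: 6/4 = 1.5 to 8/4 = 2.0.
- The TEA section also gives the later contacts as 4 to 5. The total would then be 8 to 9 and the upper ratio 9/4 = 2.25. The two statements need reconciling.

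These are planned numbers. Actual attendance could move the ratios either way.

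**Step 2. Duration ratios**

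- TEA/UC: about 26 weeks/12 weeks = 2.17.
- ITE/UC: 12/12 = 1.0. The longer period applies to TEA only.

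**Step 3. Timing of the excess**

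- To week 12, TEA has 4 treatments and usual care up to 4, a ratio of 1.0 at usual care's maximum. TEA's excess of 4 to 6 contacts therefore falls wholly between week 12 and month 6.
- ITE's excess of 2 to 4 contacts falls wholly within the first 12 weeks.

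**Step 4. Sources set side by side**

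| Source | Depends on therapist contact? | Same schedule in all arms? |
|---|---|---|
| Case report forms | Yes | No |
| Physiotherapist report | Yes | No |
| Trial co-ordinator contact | No | Schedule not stated |
| Follow-up questionnaires | No | Yes, but no item shown in Table 2 |

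The nearest Table 2 row is healthcare use, including inpatient stays, at 6, 18 and 36 months. It is not labelled as adverse-event capture and would miss events that lead to no healthcare contact.

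**Step 5. What unequal contact could do (illustration only)**

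Assume equal true event rates and a probability p that any one contact detects a given event. With k contacts, detection is 1 − (1 − p)^k. The document gives no value for p, so a range is shown, using 4, 8 and 10 contacts and no other source.

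| Assumed p | ITE/UC (8 v 4) | TEA/UC (10 v 4) |
|---|---|---|
| 0.02 | 1.92 | 2.36 |
| 0.10 | 1.66 | 1.89 |
| 0.20 | 1.41 | 1.51 |
| 0.50 | 1.06 | 1.07 |

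For example, at p = 0.10 usual care detects 1 − 0.9^4 = 0.344 and TEA 1 − 0.9^10 = 0.651, and 0.651/0.344 = 1.89.

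Now add an arm-neutral source that independently detects a share q of events. Detection becomes 1 − (1 − p)^k × (1 − q). At p = 0.10 the TEA/UC ratio is:

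- q = 0.25: 1.45
- q = 0.50: 1.23
- q = 0.80: 1.07

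The contact ratio is thus the limit as p becomes small with no other source. Any working questionnaire item pulls the ratio towards 1. The model treats an event as detectable at every contact and ignores when it occurs, so it shows direction and range and is not an estimate.

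**The case against.** The strongest reply is that the protocol already plans the remedy. It names follow-up questionnaires as a source, they go to every arm on one schedule, and co-ordinator contact does not need a treatment session either. Table 2 is weak evidence that the item is missing. It is titled as a table of outcome measures, adverse events are not listed as an outcome, and it omits other items: the Costs section says further details of work activities will be requested, and Table 2 has no such row. A journal article also leaves questionnaire wording to documents not shown here. Some arm-neutral information on harm is in the table, including worsening on the global change item and WOMAC pain at every follow-up. Finally, TEA is a longer treatment, so more recorded events in that arm may partly reflect more exposure.

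Most of this stands, and it limits the point. A reader might infer any of three stronger claims, and the protocol supports none of them:

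- *Events are gathered mainly through therapists.* Two of the four sources are not, and no weighting is given.
- *Usual care and ITE have no capture after week 12.* Scheduled therapist contact ends then, but the questionnaires are a named source and continue to 36 months.
- *The safety comparison is biased by a factor of 2 to 2.5.* No between-arm safety test is stated, and that factor needs therapist-only capture at a low detection rate.

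The objection leaves two facts in place. The therapist-dependent sources are unequal by design, and the Adverse events section relies on a questionnaire source that a list introduced as complete does not show. The possibility of greater exposure in TEA is a further reason to keep sources apart: pooled counts could not separate exposure from ascertainment.

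**Conclusion.** The point holds as a risk of differential ascertainment, not as demonstrated bias. Two of the four sources and the only described serious-event route depend on physiotherapist contact, planned at up to 2.5 times usual care in TEA and up to 2.0 times in ITE. The Adverse events section and Table 2 should be reconciled.

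The size of any distortion cannot be derived from the document. With equal true rates, the illustrative TEA/UC ratio ranges from 2.36 down to 1.07 as assumed per-contact detection rises from 0.02 to 0.50 with no other source, and it is smaller once an arm-neutral source contributes. If a common item already exists in the questionnaires, what remains is to show it and to report events by source.

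**What to change.** 1. Use one identically worded adverse-event item in the 3, 6, 9, 18 and 36 month questionnaires and in the minimum-data contact for non-responders. Show it in Table 2 with its time-points. If it already exists, adding the row is enough to reconcile the two sections.
2. Base any by-arm description of adverse events on that source.
3. Tabulate therapist- and site-reported events, including serious events, separately by arm, beside the number of contacts and the contact time. The Other data section already plans to record sessions attended and physiotherapist contact time, so no new collection is needed for this.

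The cost is slightly longer questionnaires, where the item is not already present, and one extra table in the report.
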